#### Statistical methods—additional analyses

Pairwise comparisons between COPD and healthy controls will be conducted at baseline to investigate if matching has been successful, as well as to compare the cohorts using recommended methods for parametric and non-parametric data.

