**Methods:**

COPD-HIIT is a prospective, multi-centre, randomized, controlled trial with blinded assessors and data analysts, employing a parallel-group designed trial. In phase 1, we will investigate the effects and mechanisms of a 12-week intervention of supramaximal HIIT compared to MICT in people with COPD (*n* = 92) and matched healthy controls (*n* = 70). Participants will perform watt-based cycling two to three times weekly. In phase 2, we will determine how exercise training and inflammation impact the trajectories of neurodegeneration, in people with COPD, over 24 months. In addition to the 92 participants with COPD performing HIIT or MICT, a usual care group (*n* = 46) is included in phase 2. In both phases, the primary outcomes are a change from baseline in cognitive function, cardiorespiratory fitness, and muscle power. Key secondary outcomes include change from baseline exercise tolerance, brain structure, and function measured by MRI, neuroinflammation measured by PET/CT, systemic inflammation, and intramuscular adaptations. Feasibility of the interventions will be comprehensively investigated.

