### Screening procedure

Eligibility screening will start with a telephone call (Umeå and Hasselt) or an in-person conversation (Hasselt) by a member of the research team to each participant to assess the inclusion and exclusion criteria. The responsible pulmonologist at each trial centre will, after consent, screen the medical record of the participant to assess eligibility. If the participant is eligible based on the screening, the participant will receive an accelerometer (DynaPort®, McRoberts BV, The Netherlands) to document his/her physical activity level. The participant will be instructed to wear the accelerometer on the lower back during seven consecutive days. The quantity of physical activity will be assessed using the mean number of steps per day and time spent in at least moderate-intensity physical activities. Accelerometer data consisting of ≥ 8 h/day wear time with ≥ 4 days of measurements will be considered valid [52]. In people with COPD, self-reported physical activity level measured by indicator questions from the National Board of Health and Welfare in Sweden will be used to determine eligibility when people with COPD are non-symptomatic based on mMRC dyspnoea scale or CAT. In controls, the physical activity data will be used to assess matching potential together with age and sex, and thus eligibility, and for baseline physical activity level determination. Next, the participants proceed to two–three weeks of baseline assessments where abnormal findings on examinations can lead to non-eligibility and thus exclusion.

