### Statistical methods

The change-from-baseline analyses will be performed after the last participant has completed all assessments of phase 1 and phase 2, respectively, after monitoring and data quality checks. Analyses will be performed blinded by the investigators supported by a biostatistician. All statistical tests will be conducted as two-sided, with the alpha level set at 0.05.

Baseline variables and descriptive statistics with continuous data will be presented with mean (SD) or median (IQR) as appropriate. Continuous data with normative values (for example, VO_2_peak and lung function values) will also be presented as % predicted value. Ordinal variables will be presented as median (IQR) or as *n* (%), and categorical variables will be presented as *n* (%).

A separate detailed SAP with further details about the statistical analyses including the method to handle family-wise error rate for the multiple primary outcomes will be published and finalized before the database is locked and randomization codes unblinded. In line with recommendations, it increases transparency and replicability and might be updated in response to new methods, challenges encountered during the trial, funding availabilities, and emerging evidence during the period of the trial [130, 131].

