#### Statistical methods—outcomes

For primary and secondary outcomes with continuous data, treatment effect will be estimated by mean change-from-baseline (delta-value (Δ)) with 95% confidence intervals and the effect size (ES). The between-group effects will be analysed using analysis of covariance (ANCOVA). In the ANCOVA, baseline values, age, sex, centre, and VO_2_peak will be used as covariates. In phase 1, the primary analyses will be one model for the COPD group and one model for HC. In addition, to investigate any differential effects to the interventions between COPD and HC, a two-way ANCOVA including the Group (COPD/HC) × Intervention (supramaximal HIIT/MICT) interaction will be performed. In phase 2, there will be one model with the three arms (supramaximal HIIT, MICT, and usual care). Additional details will be provided in the SAP.

The assumptions of linearity, normality of residuals, and homogenous variance will be checked using residual plots, normal quantile plots, and histograms. Violations of linearity and normality assumptions will be dealt with by transformations of the dependent variable or non-linear modelling of the independent variables. Outliers will not be removed unless there is a methodological reason for it.

Feasibility of intervention outcomes and number of responders will be described with descriptive statistics and analysed with between group (HIIT/MICT) comparisons in both the COPD (phase 1 and 2) and HC group (phase 1).

In phase 1, hospitalization and exacerbations during the intervention will be presented descriptively. In phase 2, mortality, hospitalizations, and exacerbations will be presented with descriptive statistics and analysed using Kaplan–Meier curves and Cox proportional hazard models.

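### Success of matching COPD participants to healthy controls is to be judged by baseline difference tests, which cannot show that the cohorts are matched; physical activity is the exposed variable

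*Protocol article*

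**What the plan says.** Statistical methods—additional analyses sets out the check: "Pairwise comparisons between COPD and healthy controls will be conducted at baseline to investigate if matching has been successful". The sentence then gives a second purpose and names the tool in general terms only: "as well as to compare the cohorts using recommended methods for parametric and non-parametric data". The opening part of Statistical methods fixes the level for every test: "All statistical tests will be conducted as two-sided, with the alpha level set at 0.05". No measure of balance and no tolerable imbalance is named.

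The matching variables are given under Screening procedure: "In controls, the physical activity data will be used to assess matching potential together with age and sex". Physical activity is measured by accelerometer, and the Discussion presents activity-matched controls as a strength of the trial.

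Statistical methods—outcomes gives the models. In phase 1 the primary analyses are separate models for COPD and for healthy controls. To compare the cohorts' response, "a two-way ANCOVA including the Group (COPD/HC) × Intervention (supramaximal HIIT/MICT) interaction will be performed". The covariate list reads: "In the ANCOVA, baseline values, age, sex, centre, and VO_2_peak will be used as covariates". Physical activity is not on it.

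**The concern.** Whether matching worked is a question about closeness: are the cohorts similar enough on age, sex and activity for a COPD-versus-control contrast to be interpretable? A test of no difference answers another question. Its result depends on the sample size as well as on the imbalance, so a smaller sample tends to look better matched.

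This matters because COPD participants and controls are not randomised against each other. Matching is the main design protection for the baseline cohort comparisons and for the comparison of training response between cohorts. If a non-significant test on physical activity were taken as proof of matching, a real activity difference would have no direct adjustment in the planned models. It could then be read as an effect of COPD.

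**Working it through.** The protocol gives no power, margin or sample size for the matching check, so there is no figure of its own to reproduce.

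**Inputs from the protocol**
- Cohort sizes: 92 COPD and 70 controls (Abstract, Methods).
- Two-sided alpha 0.05 (Statistical methods).

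**Assumptions**
- The cohorts are independent groups; 92 against 70 rules out complete 1:1 pairing.
- True imbalances of 0.10 to 0.50 SD, and for sex 50% in controls against 60 to 70% in COPD. These are illustrative; the protocol gives no figure.

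**Smallest imbalance the test can flag**
- SE(SMD) = sqrt(1/92 + 1/70) = 0.159.
- Threshold = t(0.975, 160 df) × 0.159 = 0.313; the normal approximation gives 1.96 × 0.159 = 0.311.
- Any observed SMD below about 0.31 is therefore non-significant.

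**Chance that a true imbalance is non-significant** (non-central t, 160 df, non-centrality = SMD / 0.1586)

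| True SMD | Non-centrality | Missed |
|---|---|---|
| 0.10 | 0.63 | 90% |
| 0.20 | 1.26 | 76% |
| 0.25 | 1.58 | 65% |
| 0.30 | 1.89 | 53% |
| 0.40 | 2.52 | 29% |
| 0.50 | 3.15 | 12% |

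Power of 80% is reached only at (1.96 + 0.84) × 0.159 = 0.44 SD.

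**Sex** (two-proportion test): 50% against 60% is missed about 76% of the time, 50% against 65% about 52%, and 50% against 70% about 26%.

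**Dependence on sample size.** In the planned Umeå participants alone (31 + 31 = 62 randomised COPD, 46 controls; Participants and recruitment), SE = sqrt(1/62 + 1/46) = 0.195. The threshold rises to 0.39, and a 0.25 SD imbalance is missed 75% of the time instead of 65%.

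**Could an equivalence test replace the difference test?** At a true difference of 0, the power of two one-sided 5% tests is about 2Φ(margin/0.159 − 1.645) − 1, taken as 0 when negative. This gives 0% for margins of 0.20 and 0.25 SD, 19% for 0.30 and 87% for 0.50. The 95% CI half-width is about 0.31 SD. These cohorts cannot demonstrate close balance by any test.

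**Which analyses depend on the matching**
- HIIT versus MICT within COPD and within controls: randomised, so not dependent.
- Group × Intervention: compares non-randomised cohorts. Age and sex are covariates; physical activity is not.
- Baseline COPD-versus-control comparisons: no adjustment is described.

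**The case against.** The strongest reply is that the protocol nowhere writes that p > 0.05 means matched, and names no specific test. The phrase about parametric and non-parametric methods may belong only to the comparison of the cohorts. That is fair: the decision rule is an inference. It is a reasonable one, because the section states the purpose of the comparisons, gives no other criterion and sits under a general 0.05 rule. Baseline summaries will also be presented, so a reader could see the size of an imbalance whatever the test shows.

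A second reply is that the choice of balance measure belongs in the SAP. The absence of a numerical bound is indeed no fault here. The point is narrower: the section names a tool unsuited to the purpose it states.

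A third reply concerns harm, and most of it stands. A reader might infer that the primary results are at risk, or that an age difference could pass unadjusted into the training-response comparison. The protocol supports neither. The primary models are within cohort and randomised, and age and sex are in the ANCOVA. Matching is applied when controls are enrolled, and no analysis is run, dropped or altered according to the later check. Because HIIT and MICT are randomised within each cohort, an activity imbalance distorts the interaction only if activity modifies the HIIT-versus-MICT contrast. Adjustment for VO2peak may also absorb part of it.

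Finally, the percentages rest on assumed imbalances and on treating selected controls as an independent sample. They show how weak the check is; they are not error rates of this trial.

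**Conclusion.** The point holds in a limited form and is minor. Difference tests at 0.05 cannot establish that the cohorts are matched. At 92 against 70, imbalances of 0.20 to 0.30 SD would go unflagged in about 76% to 53% of cases, given independent groups and those illustrative imbalances. The exposed parts are the baseline cross-sectional comparisons and, for physical activity alone, the Group × Intervention analysis. The randomised within-cohort comparisons are unaffected. That a non-significant result will be taken as successful matching is inferred from the absence of any other criterion, not stated.

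**What to change.** In Statistical methods—additional analyses, replace the significance tests of matching by a description of balance on age, sex and physical activity: SMDs, with a difference in proportions for sex, each with a 95% CI. State that successful matching will not be inferred from a non-significant p-value. Keep hypothesis tests for the cross-sectional outcome comparisons.

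Whatever the balance shows:
- report the Group × Intervention model also with baseline physical activity and its interaction with intervention; the interaction term is needed because only effect modification by activity can distort this contrast;
- report the cross-sectional COPD-versus-control comparisons also adjusted for physical activity, age and sex.

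A pass/fail bound on the SMD is not advised. With a bound of, say, 0.25 (an assumed value) and SE 0.159, a true imbalance of 0.25 SD would still pass about 50% of the time, and a perfectly balanced variable would fail about 12% of the time. Unconditional adjustment avoids that lottery.

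The cost is a few sentences, a changed column in the baseline table and a few extra model terms. All the variables are already collected. The downside is that some variables may have to be reported as imperfectly matched.

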#### Statistical methods—analysis population, missing data, and sensitivity analyses

In line with recommendations [43], both adjusted and unadjusted analyses will be presented. Analyses will employ the intention-to-treat principle when applicable, meaning that all participants randomized, whether they receive their allocated intervention or withdrew from the trial, will be included in the analysis. Analyses will be performed using multiple imputation by chained equations (MICE) for missing data. Possible violation of missing at random assumption will be investigated through a sensitivity analysis, exploring plausible scenarios of missingness during the imputation procedure. The imputation will be done separately for each intervention arm. In addition, a per-protocol analysis (defined as ≥ 75% attendance rate as well as no exacerbations during the last 2 weeks prior to follow-up assessment), and a complete case analysis (including participants with complete outcome measurements independent of attendance rate) will be reported.

### Monitoring and safety

Participants will be monitored by instructors and assessors during training sessions and outcome assessments to identify symptoms or signals that would require interruption of the session or exclusion from the trial. Blood oxygen saturation and blood pressure measurements will be taken if deemed necessary. The trial centre teams have had on-site visits prior to the start of the intervention to ensure standardization across centres. Research progress will be monitored closely, and adjustments to individual tasks will be made if necessary, using monthly group meetings across participating centres.

Reasons for immediately stopping an outcome assessment or training session, and examples of possible adverse events, include chest pain, intolerable dyspnoea, leg cramps, staggering, dizziness, diaphoresis, and pale or ashen appearance. When monitored via ECG, blood pressure, and saturation during cycling tests, additional indications to terminate exercise are defined [133].

An external data monitoring and safety committee (DMC) will consist of an independent group of medical doctors and physiotherapists that will monitor patient safety and treatment efficacy. All adverse events will be reported to the DMC every third month of the project, which could result in the discontinuation of the trial for the individual participant. The DMC will be responsible for decisions related to stopping the trial if any SAE happens during the trial period. There are no interim analyses planned other than the sample size re-estimation in phase 2. There is no other pre-planned auditing of the trial. The funders might do project reviews and financial audits, independent from the sponsor.

#### Protocol amendments

Any modifications to the protocol which may impact the conduct of the trial, potential benefit of the patient or may affect patient safety, including changes of study objectives, trial design, participant population, sample sizes, trial procedures, statistical analyses, or significant administrative aspects will require a formal amendment to the protocol, or if adequate, be included in the SAP. Such amendments will be agreed upon by the research group with the final decision by the PI and, if needed, approved by the Regional/Local Ethics Committees. Administrative changes of the protocol (e.g., minor corrections and/or clarifications) that have no effect on how the trial is conducted will be agreed upon by the research group with the final decision by the PI and documented and presented upon publication.

#### Ancillary and post-trial care

Participants that are enrolled into the trial are covered by a local insurance that will cover potential additional healthcare needs that arise because of trial participation, such as adverse events during the intervention.

### Access to data

Access to data is based on the established collaboration agreements including material and data transfer agreements.

### Dissemination plans

The results from this trial will be disseminated regardless of the magnitude or direction of effect. Results from this trial will be submitted for publication in peer-reviewed journals and presented at national and international conferences (e.g., European Respiratory Society Congress). We will also disseminate the results via newsletter articles, social media, and talks to clinicians, patient organizations, individuals with COPD and older healthy adults. Trial participants who are interested in receiving a summary of their own results will receive them via mail.

Actors who have contributed substantially in study design, data collection, data analysis and interpretation, manuscript preparation and critical revising, and in final manuscript version approval will be affiliated as authors according to international recommendations [134].

## Discussion

We have designed a comprehensive multicentre randomized controlled trial to investigate the effects of supramaximal HIIT compared to MICT in people with COPD and healthy controls. It is the first comprehensive trial investigating supramaximal HIIT in the COPD population. COPD-HIIT is also the first trial to, in a large sample of people with COPD, investigate global cognitive function using an extensive test battery [27], and brain health using both MRI and PET/CT scans.

The COPD-HIIT project has the potential to induce a shift in the therapeutic approach to extrapulmonary manifestations in COPD. Currently, no therapeutic modality available for COPD can effectively target multiple manifestations of the disease [9]. The advantage and novelty of the supramaximal HIIT approach entails the enabling of participants to reach supramaximal exercise intensities in a safe and feasible way. In addition to exercising at higher intensity, reducing the ventilatory burden with supramaximal HIIT will potentially allow people with COPD to experience multiple extrapulmonary benefits. This is partly via effective activation of the AMPK-PGC-1α-BDNF pathway, beneficial for mitochondrial and brain health. Also, the supramaximal HIIT modality is promising for increased adherence given that it might reduce dyspnoea, is shorter in duration compared to MICT, and in our preliminary data, was preferred by most participants [17].

A strength in the COPD-HIIT project is the international and interdisciplinary research collaboration with state-of-the-art infrastructures. Additionally, our trial’s inclusion of objectively measured physical activity matched healthy controls distinguishes itself from prior research on exercise and extrapulmonary manifestations in COPD. This feature will contribute valuable insights to the ongoing debate regarding the impact of COPD on exercise response and adaptation [4, 135] . Another strength of the trial is the carefully planned intervention, guided by the fundamental training principles and the CERT checklist [42].

As all randomized controlled trials, this trial has some challenges and limitations. While different exercise intensities will be investigated, we will not be able to determine the optimal dose of the exercise regimens, but only draw conclusions on the prescribed doses. Maintaining a high attendance over the course of 2 years is a challenge. Trial withdrawals and missing data, as well as random differences at baseline are factors than can interfere with the interpretation of the intervention’s effects. However, data imputation, randomization, and adjustment for covariates will to some extent mitigate these challenges.

## Trial status

This manuscript reports protocol version 1.1 finalized at 11 April 2024. Ethical approval has been obtained for all procedures in Umeå, Sweden, and in Hasselt, Belgium. The trial started enrolling participants on the 9th of November 2023 in Umeå, Sweden and on the 16th of September 2024 in Hasselt, Belgium. At the time of manuscript submission (3 January 2024), 14 participants had been enrolled. At manuscript acceptance, 17th September 2024, 51 participants have been enrolled. Data collection for phase 1 is expected to take place over 2–3 years, while phase 2 is expected to take place over 5 years.

## Data Availability

We aim to share all the de-identified individual participant data that underlie results in a publication in an open data repository, if this will be possible given regulations and agreements at the time. Data will be shared 6-months after publication.

## Abbreviations

5-STS: Five times sit-to-stand test
AE: Adverse event
AMPK: Adenosine monophosphate-activated protein kinase
ATS: American Thoracic Society
BCST: Borg cycle strength test
BDNF: Brain-derived neurotrophic factor
BMI: Body mass index
CAT: COPD Assessment Test
CERT: Consensus on exercise reporting template
CR10: Category ratio 10
CRF: Case report form
CRQ: Chronic respiratory disease questionnaire
COPD: Chronic obstructive pulmonary disease
CONSORT: Consolidated standard reporting of trials
CVD: Cardiovascular disease
CPET: Cardiopulmonary exercise test
CS: Citrate synthase
DTI: Diffusion tensor imaging
DMC: Data monitoring committee
ECG: Electrocardiogram
EDTA: Ethylenediaminetetraacetic
ELISA: Enzyme-linked immunosorbent assay
ERS: European Respiratory Society
EQ: EuroQol
F: Force
FLAIR: Fluid-attenuated inversion recovery
FNDC5: Fibronectin type III domain-containing protein 5
GOLD: Global initiative for chronic lung disease
HADS: Hospital Anxiety and Depression Scale
HADH: 3-Hydroxyacyl coenzyme A dehydrogenase
HbA1C: Glycated haemoglobin
HIIT: High-intensity interval training
HDL: High-density lipoprotein
HRQoL: Health-related quality of life
HRV: Heart rate variability
hs-CRP: High-sensitivity C-reactive protein
IGF-1: Insulin-like growth factor 1
IL: Interleukin
KYN: Kynurenine
KYNA: Kynurenine acid
KAT1-4: Kynurenine aminotransferase
LDH: Lactate dehydrogenase
LDL: Low-density lipoprotein
MAP: Maximal aerobic power
MCID: Minimal clinically important difference
MDC: Minimal detectable change
MICT: Moderate-intensity continuous training
mMRC: Modified Medical Research Council Dyspnea scale
MRI: Magnetic resonance imaging
MoCA: Montreal Cognitive Assessment
MPO_6_: Maximum mean power output for 6 s
NRF1: Nuclear respiratory factor 1
NRF2: Nuclear respiratory factor 2
P: Power
PET/CT: Positron emission tomography/computed tomography
PGC-1α: Peroxisome proliferator-activated receptor gamma coactivator 1-alpha
PGC-1β: Peroxisome proliferator-activated receptor gamma coactivator 1-beta
PFK: Phosphofructokinase
PPAR-α: Peroxisome proliferator-activated receptor-alpha
qPCR: Quantitative polymerase chain reaction
REDCap: Research electronic data capture
RHR: Resting heart rate
RMSSD: Root of the mean square of successive R–R interval differences
RPE: Rating of perceived exertion
SAE: Severe adverse event
SAP: Statistical analysis plan
SCPT: Stair climb power test
SDH: Succinate dehydrogenase
SDNN: Standard deviation of N–N intervals
SPIRIT: Standard Protocol Items: Recommendations for Interventional Trials
SST: Serum separator tube
TFAM: Mitochondrial transcription factor A
TIDieR: Template for intervention description and replication
TNF-α: Tumour necrosis factor-alpha
V: Velocity
VEGF: Vascular endothelial growth factor
VO_2_peak: Peak oxygen consumption
